## Abstract

**Background:**

There is high prevalence of back pain and neck-shoulder pain among blue collar workers in Denmark. Excessive physical exposures such as heavy lifting or working with bended or twisted back are risk factors for back pain among workers in the construction industry. Technical evaluation of awkward postures and kinematics of upper/ lower extremities (accelerometry) during work combined with the level of muscular activity (EMG) and video recordings can improve quantification of physical exposure and thereby can facilitate designing preventive strategies. Participatory ergonomics potentially increase the success of interventions aimed at reducing excessive physical exposures. The objectives of this study are to; 1) determine which work-tasks in selected job-groups involve excessive physical load of the back and shoulders during a normal working day (measured with accelerometers, EMG and video recordings). And 2) investigate whether a participatory intervention can reduce the excessive physical workloads, drawing on measurements from phase 1.

**Methods/Design:**

A two-armed parallel-group, single-blind, cluster randomized controlled trial with allocation concealment will be conducted in the Danish construction industry. Approximately 20 construction gangs (≈80 subjects) will be recruited and randomized at the cluster level (gang). We will record in situ physical workload using technical measurements (EMG, accelerometers and video recordings) during a working day before and after the intervention. Based on these measurements a physical load matrix for each worker will be developed.

The participatory intervention consist of three workshops: 1) One at baseline, involving presentation of video clips of the work-tasks with excessive physical load customized for each gang, followed by a participatory development of solutions on how to reduce excessive workloads, leading to development of an action plan on how to implement these solutions at the workplace. 2) A second workshop where the implemented solutions will be further developed and qualitatively evaluated during group discussions. 3) A final workshop at follow-up to enhance long-time organizational sustainability of the implemented solutions.

**Discussion:**

The results will provide knowledge about the level of physical exposure of the back and shoulders during specific work tasks in the construction industry, and will provide information on options to implement participatory interventions aiming at reducing excessive physical workload.

**Trial registration:**

ClinicalTrials.gov (NCT02498197), registered 29 June 2015.

## Background

Musculoskeletal disorders (MSD), especially low back pain and neck-shoulder pain, constitute a substantial problem in the working environment [1–8]. MSD can lead to physical disability, long term sickness absence [9, 10] and early retirement [11]. Prevention of MSD should have high priority as recurrent pain is common once an initial episode has occurred [12–15]. MSD have a complex etiology and are affected by individual factors as well as psychosocial and physical exposures in the working environment [16]. High physical work demands increase the risk of MSD [17, 18], e.g. heavy lifting is a risk factor for developing low back pain [19, 20], and a relationship between working with a bended or twisted back and low back pain has been demonstrated [19]. In line with this, a recent health impact assessment based on a meta-analysis using quantitative exposure information found evidence that heavy lifting during work increases the risk of low back pain [21]. This research document that lifting loads of more than 25 kg and lifting with a frequency of more than 25 lifts per day increased the annual incidence of low back pain by 4.32 % and 3.50 %, respectively [21].

Certain occupations are particularly exposed to physical risk factors. Among workers in the construction industry there is a high degree of heavy lifting combined with bending and twisting of the back [18]. A Danish survey “Work Environment & Health” from 2012 showed that 68 and 67 % of concrete workers and carpenters, respectively, work with a bended or twisted back for more than a quarter of their total working time, and 41 % and 48 %, respectively, state that the load during a typical lift exceeds 16 kg [22]. Moreover, 40-50 % of these workers report pain in the body several times a week [22].

Besides low back pain there is high prevalence of neck-shoulder pain among blue collar workers, i.e., in an Danish cohort study 29 % reported severe pain in the neck-shoulder region [23]. Accordingly, physical risk factors for neck-shoulder pain like high physical load, working with raised arms, repetitive movements [24] and working in awkward positions [25] are common in construction work.

Existing knowledge about the dose–response relationship between physical risk factors during work and MSD is almost exclusively based on self-reported data on work-load, or derived from biomechanical laboratory studies with static postures rather than dynamic lifting performed under actual working conditions [26]. Thus, obtaining technical measured information on physical work exposures during the working day may provide a more realistic picture of the physical risk factors compared with self-reports or laboratory measurements. The development of small wearable sensors has enabled measurements of physical load in situ during an entire working day [27–29]. A recent study, using this type of measurements during a working day on 200 blue-collar workers with physical strenuous work, found a positive correlation between perceived physical exertion and relative muscle load measured with surface electromyography (EMG) of the upper trapezius muscle during daily lifting tasks [27]. Furthermore, technical measurements using EMG [27], accelerometers [30], and video recordings [31, 32] or a combination of the three techniques have been used separately or in different studies to quantify physical load in workers with strenuous work [33, 34]. However, to our knowledge no intervention studies have employed these methods simultaneously to obtain detailed information about kinematics and level of muscle activity during a working day. The use of such methods to reduce excessive physical workload would likely make interventions more specific and meaningful for workers both individually and in work groups.

In Denmark, construction work is usually organized in small groups with a high degree of self-organization called construction gangs. This structure makes it possible to coordinate, collaborate and make changes in small teams, i.e. during a participatory intervention. Participatory interventions draw on workers experiences and knowledge of work to tailor the intervention to the context, culture, as well as the psychosocial and organizational conditions of the workplace. Participatory interventions that engage the workers and tailor the work to the employees’ skills and capacity, have shown to support return to work after disease due to low back pain [35]. Likewise, reduced physical work load among workers with manual handling tasks has been reported in response to a participatory intervention emphasizing the use of technical assistive devices [36]. The European Agency for Safety and Health at Work recommends employees being involved in the processes at the working site to increase motivation, and to help the employer identify solutions for solving health and safety problems [37]. Because participatory approaches have been shown to increase employee ownership and support [38], many researchers recommend participatory interventions to increase the likelihood for a successful outcome and sustainable implementation [39–42]. A recent participatory intervention based on measurements from 10 min cleaning tasks revealed a decreased cardiovascular workload, and a more variable pattern of muscle activity among cleaners [28]. The latter has previously been considered preventive for developing musculoskeletal pain [43]. However, there is a need to investigate whether such knowledge can be adapted to the construction industry, where work is changeable i.e. in terms of working tasks and conditions on varying work sites.

In this cluster randomized controlled study we implement a participatory intervention involving construction workers and managers to emphasize organizational engagement. The intervention combines technical measurements of physical work load with surveys on psychosocial and organizational conditions to develop solutions for reducing physical risk factors during construction work. The objectives of this study are to; 1) determine which work-tasks in selected job-groups involve excessive physical load of the back and shoulders during a normal working day (measured with accelerometers, EMG and video recordings). And 2) investigate whether a participatory intervention can reduce the excessive physical workloads, drawing on measurements from phase 1. We hypothesize that a participatory intervention involving both leaders and workers will lead to identifying solutions (technical, physical, organisational, etc.) to which both leaders and workers are mutually committed to (ownership), which will lead to a reduction in workload and thereby the physical risk factors for developing MSD in the construction industry.

## Methods

### Study design

A two-armed parallel-group, single-blind, cluster randomized controlled trial with allocation concealment will be conducted in a part of the Danish construction industry. Clusters will be construction gangs typically consisting of 3-5 workers. The study setting will be on the actual working sites of the workers. Data collection is expected to take place from autumn 2015 to summer 2016, and will be completed in two phases: 1) technical measurements and questionnaires to determine the tasks with excessive physical workload for groups of construction workers. 2) a cluster randomized controlled trial that investigates whether the participatory intervention can reduce the physical load of the back and shoulders during the working day.

### Phase 1 – detection of the physical load

The physical load during the working day will be determined using technical measurements recorded simultaneously; EMG and awkward postures and kinematics of upper/lower extremities (accelerometers) which has been used in previous studies [27, 28] as well as video recordings. The equipment measuring EMG and awkward postures and kinematics will be mounted under the working clothes of workers to minimize inconvenience. Based on these measurements we will develop a load matrix for each worker in the study that will be the basis for the detection of which working tasks evoke excessive physical load. Work tasks with measurable excessive load will be identified and selected for inclusion in the workshop. During the workshop the video recordings of the work tasks with excessive physical load will be shown to the gang and their managers.

### Phase 2 – workshops and implementation

The intervention will apply a cluster randomized controlled design with technical measurements of the physical load during the working day at baseline and at 3 and 6 months follow-up. The control group will receive flyers with information on health, lifting technique and safety procedures.

The intervention will consist of three workshops over a period of two months (Fig. 1). The workshops are fashioned in an experimental design inspired by methods for participation drawing on action and interactive research, emphasizing open dialogue and the inclusion of both workers and managers [47]. The inclusion of both groups is important to increase chances for organizational anchorage and continuity of solutions as construction workers often change work place and employment, and research has underlined the engagement of management as an important factor for successful organizational implementation of health and safety initiatives [48, 49].

**Fig. 1 Fig1:**
[figure not shown]
*Workshop 1:* at baseline, an opening workshop with presentation of video recordings, followed by participatory development of possible solutions on how to reduce the excessive workloads, and development of an action plan on how to implement the suggested solutions. *Workshop 2:* The solutions implemented will be qualitatively evaluated during group discussions and adjusted if necessary. *Workshop 3:* Follow-up workshop where planning on how to sustain the implemented solutions can be achieved

**Fig. 2 Fig2:**
[figure not shown]
Study design and participant flow

At the baseline workshop, recordings will be presented showing work tasks with excessive physical load customized for each gang. These presentations will be followed by participatory development including individual and group-based idea-generation and discussions of possible solutions on how to reduce excessive workloads. The outcome of the first workshop is the development of an action plan on how to implement suggested solutions. At the second workshop, the solutions implemented will be qualitatively evaluated during group discussions among gang members and their leaders and adjusted with the aid of researchers and expert consultants on construction health and safety if necessary. A third workshop with gang members and their managers, where focus is on planning how long-time continuity of the implemented solutions can be achieved.

### Outcomes

The primary outcome of the present study is the change from baseline to follow-up in frequency of events with excessive physical load. Secondary outcomes are those obtained from the questionnaires, including psychosocial and organizational conditions based on the musculoskeletal pain intensity during the last week (scale 0-10), work ability index, self-efficacy and social capital (within gangs, between gangs and between gangs and their leader).

### Study population

We aim to recruit and randomize 20 construction gangs (≈80 subjects) into an intervention group or a control-group in a 1:1 allocation ratio (Fig. 2). Age and gender will reflect the distribution in the construction industry, which means that there will be a majority of men included in the study.

Inclusion criteria will be: Full time construction workers who can read and understand Danish. The type of work must include manual work that involves lifting. Exclusion criteria will be: life-threatening diseases, hypertension >160/100 mmHg, and pregnancy.

### Recruitment

The majority of participants will be recruited during 2015, and will occur in collaboration with The Danish Construction Association and consultants from The Safety and Health Preventive Service Bus for the Construction Sector. The reason for involving these institutions in the recruitment phase is that they have intimate knowledge of the construction industry and contacts to companies. The subjects will get their lost earnings covered for the time they use for participation.

### Sample size

Concerning outcome measurements, we expect EMG to be the method with lowest reliability [50]. Consequently, the power calculation is based on EMG. The primary outcome of the present study is the change from baseline to follow-up in frequency of events with excessive physical load. As the methods are new in the way that they are used simultaneously, we do not have any information on the reliability of the primary outcome, and have thus based the power calculations on closely related data. The power calculation shows that to demonstrate a reduction in 20 % in normalized EMG (nEMG) with a SD of ≈20 % in normalized EMG between individuals (based on previous research with EMG during a full working day [29]), and a type I risk of 5 % and a power on 80 % the sample size should have a minimum of 17 subject in each group. With an inflations factor of 1.5 due to the cluster randomization it will require 26 subjects in each group. For generalizability of the results we wish to include at least 10 construction gangs of 3-5 subjects in each group corresponding to approximately. 40 subjects.

### Randomization and blinding

An independent researcher will perform a block randomization on clusters of construction gangs of typically 3-5 workers. The researchers involved in the study will not be aware of the block size. Blinding of the researchers performing the measurements during the working day as well as the subjects of the study is not possible. However, as the measurements are technical, this will likely only introduce minimal bias to the results of the study. Moreover, data analysts and statisticians will be blinded to group allocation. The block randomization will be stratified for job group.

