### Statistics

Statistical analyses will be performed using the SAS statistical software (SAS Institute, Cary, NC). The change in frequency and duration of events with excessive physical workload will be evaluated using a repeated-measures linear mixed model with *group*, *time* and *group by time* as independent variables. Participants nested within gangs will be entered as random effect to account for clustering. Analyses will be adjusted for baseline values of the number of events with excessive physical workload, gender and age. All statistical analyses will be performed in accordance with the intention-to-treat principle, i.e. including all available data in the analyses regarding actual participation or dropout. If participants do not show up for the intervention they will still be offered participation in the follow-up measurements. A P-value below 0.05 will be accepted as statistically significant. Outcomes will be reported as between-group least mean square differences with 95 % confidence intervals at follow-up.

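### Gangs are randomised within job groups but the stated model omits job group, so the reported standard error is somewhat too large and the test conservative

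*Protocol article*

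**What the plan says.** Under Randomization and blinding, the unit of allocation is the gang: "An independent researcher will perform a block randomization on clusters of construction gangs of typically 3-5 workers". The same section adds that "The block randomization will be stratified for job group". The number of job groups is not given. Under Study population the target is stated as: "We aim to recruit and randomize 20 construction gangs (≈80 subjects) into an intervention group or a control-group in a 1:1 allocation ratio".

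Under Statistics, the primary outcome is to be "evaluated using a repeated-measures linear mixed model with" group, time and their interaction. Clustering is handled as follows: "Participants nested within gangs will be entered as random effect to account for clustering". The covariates are then listed: "Analyses will be adjusted for baseline values of the number of events with excessive physical workload, gender and age". Job group is not among them. Two of the listed covariates, gender and age, played no part in the randomisation, while the one factor that did is absent.

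**The concern.** Stratifying by job group makes the arms more alike on job group than simple randomisation would. A model without that factor does not know this. It treats differences between job groups as random variation between gangs, which could have fallen unevenly on the two arms, and charges them to the error of the treatment contrast. The gang random effect does not replace the stratum term, because it is the variance component into which those differences fall.

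Job group could plausibly predict the outcome. The first objective of the trial is to find out which tasks in selected job groups produce excessive load, and a stratification factor is normally chosen because it is expected to matter. With only about 20 randomised units, an overstated standard error could make a real reduction in events harder to show.

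**Working it through.** **The plan's own figure.** The Sample size section assumes a 20 % reduction in normalised EMG, "with a SD of ≈20 % in normalized EMG between individuals", type I error 5 % and power 80 %. A two-sided two-sample t-test gives 17 per group (power 0.807 at 17, 0.781 at 16). Then 17 × 1.5 = 25.5, rounded up to 26. The stated 17 and 26 reproduce, and the point made here does not change them.

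**Implied intraclass correlation.** The article does not say how the factor 1.5 was obtained. If it is the usual design effect with m = 4 workers per gang (80/20), then 1 + (4 − 1) × ICC = 1.5, so ICC = 0.5/3 = 0.167.

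**Share of error that lies between gangs.** In units of the total variance, a gang mean has variance 0.167 + 0.833/4 = 0.375. The between-gang share is 0.167/0.375 = 0.44.

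**Effect of omitting job group.** Let R be the share of the between-gang variance, after baseline adjustment, that job group explains. No value is given, so R is assumed. The interval is wider than needed by the factor 1/√(1 − 0.444 R):

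- R = 0.1: 1/√0.956 = 1.02
- R = 0.2: 1/√0.911 = 1.05
- R = 0.3: 1/√0.867 = 1.07
- R = 0.4: 1/√0.822 = 1.10

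Gang size matters little. With m = 3 the factor 1.5 implies ICC = 0.25 and a share of 0.25/(0.25 + 0.75/3) = 0.50, giving 1.03 to 1.12. With m = 5 it implies ICC = 0.125 and a share of 0.125/(0.125 + 0.875/5) = 0.42, giving 1.02 to 1.10.

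**Simulation.** 20 gangs of 4 were randomised 1:1 within 2 or 5 equal job groups, with 1,000 runs per setting. Assumed: job group is 10 % or 30 % of outcome variance, ICC 0.167 within job groups, baseline to follow-up correlation 0.5, one follow-up, true effect 0 or 0.6 SD. The fitted model had a random gang intercept and baseline adjustment, with and without job group.

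- *Job differences equally visible at baseline, job group omitted.* The mean reported standard error is about 2 to 13 % above the true SD of the estimate (for example 0.223 against 0.198, ratio 1.13). Type I error is 0.025 to 0.039, and power is 2 to 8 points lower than with job group included (for example 0.746 against 0.829).
- *Job differences not visible at baseline at all, job group omitted.* The standard error is roughly 20 to 70 % too large (for example 0.267/0.222 = 1.20; 0.324/0.190 = 1.71). Type I error is 0.001 to 0.023, and power is 12 to 46 points lower.
- *Job group included.* The standard error is within about 4 % of the true SD, and type I error is 0.041 to 0.053.
- *Job group explains nothing.* Power is unchanged with 2 job groups (0.661 both ways) and about 2 points lower with 5 when it is included (0.665 to 0.643).

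The true SD of the estimate is nearly the same either way (0.198 without job group, 0.199 with it, in the first example). Only the reported standard error differs.

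**Why the second setting is so much worse.** There, job group is a far larger share of the residual between-gang variance than the 10 to 40 % used above. At a 10 % job share, the other between-gang variance after baseline is 0.167 × 0.9 × (1 − 0.5²) = 0.113, so job group is 0.1/0.213 = 47 %. At a 30 % share it is 0.167 × 0.7 × 0.75 = 0.088, so job group is 0.3/0.388 = 77 %.

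**Cost in degrees of freedom.** There are about 20 − 2 = 18 gang-level degrees of freedom. Five job groups use 4 of them, leaving 14. The critical t rises from 2.10 to 2.14, about 2 % in width.

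**The case against.** The best defence is that the model already adjusts for baseline events. A difference between job groups in their usual level of exposure is largely the kind of difference that this adjustment absorbs. The only figures by trade, in the Background, are close: 68 % and 67 % of concrete workers and carpenters work with a bent or twisted back for more than a quarter of the time, and 41 % and 48 % report typical lifts above 16 kg. The error is on the safe side. The plan also has a cushion on its own calculation, with 26 per group required and about 40 intended. And the remedy is not free: with five job groups its 2 % cost cancels the gain at R = 0.1.

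Most of this stands as a limit on size. It does not remove the mismatch. Baseline absorbs only the part of the job differences that persists, and the Strengths and limitations section says that construction work varies a great deal, although it does not say that it varies by job group. The survey figures are self-reports from two trades, not event counts. The cushion rests on a surrogate for the primary outcome. Nor is this a detail left to a fuller plan: the article commits to a specific list of covariates.

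Two stronger readings are tempting. A reader might apply 1/√(1 − R) to the whole interval and infer that it is 5 to 29 % too wide for R from 0.1 to 0.4 (1/√0.9 = 1.05; 1/√0.6 = 1.29). That treats between-gang variance as the only source of error. With about four workers per gang, more than half of the variance of a gang mean is within-gang and is untouched by job group. A reader might also infer that the precision gained by stratifying is lost outright, or that the result is biased or prone to false positives. The simulation shows otherwise: the arms remain balanced, the estimate is about as precise as before, and the test rejects too seldom.

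**Conclusion.** The point holds as a minor mismatch between design and analysis. The omission itself is certain from the text; its size is not. About 2 to 10 % of unnecessary interval width is a reasonable working figure. It rests on three assumptions: that 1.5 is a design effect at four per gang, that the resulting ICC still applies after baseline adjustment, and that job group explains 10 to 40 % of what remains between gangs. The much larger losses in the simulation require job-group differences that baseline misses entirely, for which the article offers no evidence. The simulation also uses a single follow-up and a continuous outcome, so it indicates direction and order of size for the planned repeated-measures analysis, not exact values.

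**What to change.** Add job group, as defined for the randomisation strata, as a fixed effect in the primary model and in the models for the secondary outcomes. Before allocation is revealed to the analysts, set down a rule for pooling any job group that contains a single gang. Such a gang offers no comparison between arms within its stratum, so a separate term for it would remove it from the treatment contrast. Pooling means that the model factor is slightly coarser than the randomisation factor, and the plan should say so.

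The change needs no new data, because job group must be known at randomisation, and it alters neither the sample size nor the conduct of the trial. It uses one gang-level degree of freedom fewer than the number of job groups, out of about 18. Since the number of job groups is not stated, the plan should give it, so that this cost can be seen.
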